**Figure 1 F1:**
[figure not shown]
**Research procedure**. After informed consent is obtained, 2/3 of all parent-child dyads will be randomized into the experimental arm and 1/3 into the control arm. Parents and children are asked to fill out questionnaires (parent: TSCYC, CBCL, Questionnaire about duration and severity of domestic violence, demographic questionnaire, IES-R, HADS, PSI; child: CDI, TSCC, Questionnaire for children how to cope with difficult situations) at the first assessment (T1). A week later the program starts for all parents and children. One week (T2) and six months (T3) after the end of the program parents and children who take part in the study are again invited to fill out questionnaires and participate in two observation tasks (FIT and AEED). To check up on parents in the period between T2 and T3, parents are contacted by phone two times. At all assessments the teacher is also sent a questionnaire.

Parents receive €15,- after completing the first assessment, €25,- after participating in the program and completing the second assessment and €40,- after completing the follow up assessment. Children receive a gift after each assessment.

### Blinding

Parents, children, social workers as well as the researchers are blind to group allocation until two weeks before the start of the program. The condition is not disclosed earlier to avoid a bias in the intake procedure because of prior knowledge about the condition. Parents and children agree to participate in the study before randomization and without knowing in which arm they will be enrolled. Both programs are presented as useful programs by discussing the specific and/or nonspecific factors that can be of benefit to children and parents exposed to interparental violence. Every ID-number assigned to a parent-child-dyad is independent of the condition. The researchers coding the observation tasks and analyzing the data will be blind to the group condition of parents and children, as well as assessment (T1, T2, T3).

### Interventions

#### Intervention program 'En nu ik...!' ('It's my turn now!')

The child sessions of the program 'En nu ik...!' are based on the psycho-educational secondary preventive intervention program 'Kids' Club' [20]. Changes in the original manual, with respect to topics and methods have been made. 'En nu ik...!' was further developed by including nine parallel group sessions for parents. Theoretical conceptualizations used in the development of this program are trauma theory [12] and attachment theory [18]. Child sessions of 'Kids' Club' have been adapted for use in the Netherlands by a consortium formed by the Women Shelter in Amsterdam (Blijf Groep), the Centre of Youth Care in Amsterdam (BJAA/SO&T), social work and mental health care services in Amsterdam (the Netherlands). The program consists of nine group sessions of 90 minutes each for children and nine parallel group sessions for their caregiving custodial parent. Each group has a maximum of eight children or parents. Usually a social worker together with a mental health care professional act as therapists. Therapists are trained in giving this standardized program and follow a protocol for every session. Therapists receive supervision during the program.

##### Children's sessions

The program 'En nu ik...!' has three main intervention goals for children:

 1) to (make a start with) process(ing) the interparental violence experiences

 2) to learn how to differentiate and express emotions

 3) to learn how to cope with feelings and problems in a different (non-violent) way

 All sessions follow a predictable structure. Every week the children start in a circle and hold hands to greet each other. Then they are asked how they feel today and a short story about different topics related to interparental violence and emotion recognition is read and talked about. After that the children have a break and drink and eat something before they start with the activity of the week. Every activity is related to the topic covered that week and varies per session. The session is finished with a gross motor game to relieve tension after a possible strenuous session. Children and parents are reunited and encouraged to share what they have done during the session. Focal topics are: session 1) getting to know each other and recognizing emotions; 2) emotions; 3) sadness or happiness and a safe place; 4) anger; 5) conflicts and loyalty; 6) violence, conflicts and contact with the other parent; 7) secrets and safety; 8) the future, and 9) saying goodbye and evaluation.

##### Parents' sessions

Goals for the parents' sessions are to learn how to become more sensitive in supporting their children who deal with difficult experiences and emotions, and to take the perspective of the child who witnessed interparental violence. Although the parent sessions are not aiming to help parents process their own experiences, sharing of experiences is not discouraged either and a supportive group atmosphere is created. Focal topics of the sessions are: 1) getting to know each other; emotions; violence; 2) parenting: the parenting role versus the role of the child; 3) a safe place, offering safety, making compliments; 4) coping with feelings of anger and sadness; 5) coping with feelings of guilt, shame and loyalty; 6) safety, conflicts and contact with the other parent; 7) social contacts and social network; 8) unspecified theme, depending on the needs of the participants, and 9) saying goodbye and evaluation.

#### Control program 'Jij hoort erbij' ('You belong')

For this study, an alternative control program was developed, based on a content analysis of nonspecific factors within the intervention program [23]. Basic elements of interventions, including positive attention from a therapist, positive expectations and hope, distraction and social support and recognition among group participants were deemed present in the intervention program, and were therefore built into the design of the control program as well; no specific attention is paid to the interparental violence. The reasons for the development of a control program were 1) to evaluate the need for specific factors in interventions, 2) to be able to monitor families in both arms equally well over time, and 3) to prevent higher drop-out rates in the control arm.

The control program follows the same structure as the intervention program and also consists of nine sessions of 90 minutes each for children and nine parallel group sessions for their caregiving custodial parent. The maximum group size is eight participants. Therapists are a clinical child psychologist/pedagogic specialist and a pedagogic specialist in training, for both parents and children. Therapists are trained in giving this standardized program and receive supervision during the program.

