## Abstract

**Background:**

Children who witness interparental violence are at a heightened risk for developing psychosocial, behavioral and cognitive problems, as well as posttraumatic stress symptoms. For these children the psycho-educational secondary prevention program 'En nu ik...!' ('It's my turn now!') has been developed. This program includes specific therapeutic factors focused on emotion awareness and expression, increasing feelings of emotional security, teaching specific coping strategies, developing a trauma narrative, improving parent-child interaction and psycho-education. The main study aim is to evaluate the effectiveness of the specific therapeutic factors in the program. A secondary objective is to study mediating and moderating factors.

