**Methods/design:**

This study is a prospective multicenter randomized controlled trial across cities in the Netherlands. Participants (N = 140) are referred to the secondary preventive intervention program by police, social work, women shelters and youth (mental health) care. Children, aged 6-12 years, and their parents, who experienced interparental violence are randomly assigned to either the intervention program or the control program. The control program is comparable on nonspecific factors by offering positive attention, positive expectations, recreation, distraction, warmth and empathy of the therapist, and social support among group participants, in ways that are similar to the intervention program. Primary outcome measures are posttraumatic stress symptoms and emotional and behavioral problems of the child. Mediators tested are the ability to differentiate and express emotions, emotional security, coping strategies, feelings of guilt and parent-child interaction. Mental health of the parent, parenting stress, disturbances in parent-child attachment, duration and severity of the domestic violence and demographics are examined for their moderating effect. Data are collected one week before the program starts (T1), and one week (T2) and six months (T3) after finishing the program. Both intention-to-treat and completer analyses will be done.

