##### Parents' sessions

To be able to relate changes in outcome measures to the content of the program, also nine parents' sessions have been developed for the control program. As in the children's sessions, the focus in the parents' sessions is on creating a positive atmosphere and having a good and relaxing time together. Topics of the sessions are: 1) getting to know each other; 2) fun things to do with your child(ren); 3) healthy food; 4) do-it-yourself; 5) books to read together with your child(ren); 6) how to keep a budget; 7) creative activities; 8) bingo, and 9) saying goodbye and evaluation.

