##### Treatment integrity

At least one, but preferably more parent and child sessions, of the intervention and control programs are randomly chosen and video-taped to be able to assess if the program is carried out according to the protocol. Ten percent of the video tapes will be randomly selected to be coded.

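### Therapist profession differs by arm as described, so therapist type is largely confounded with the program content whose effect the trial wants to isolate

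*Protocol article*

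**What the plan says.** **Aim.** The Abstract (Background) states: "The main study aim is to evaluate the effectiveness of the specific therapeutic factors in the program". The control program is the tool for this. It keeps the structure of the intervention and removes the specific factors.

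**Claimed comparability.** The Abstract (Methods/design) states: "The control program is comparable on nonspecific factors by offering positive attention, positive expectations, recreation, distraction, warmth and empathy of the therapist". The control program's section on parents' sessions shows that effects are to be traced to content: "To be able to relate changes in outcome measures to the content of the program, also nine parents' sessions have been developed for the control".

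**Staffing, intervention arm** (Interventions): "Usually a social worker together with a mental health care professional act as therapists". On preparation: "Therapists are trained in giving this standardized program and follow a protocol for every session". These therapists are also supervised.

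**Staffing, control arm** (Control program): "Therapists are a clinical child psychologist/pedagogic specialist and a pedagogic specialist in training, for both parents and children". On preparation: "Therapists are trained in giving this standardized program and receive supervision during the program".

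**Safeguards.** The section on control variables names two things that are measured so that change can be credited to the program: intervening life events and treatment integrity. For integrity, sessions in both arms are taped "to be able to assess if the program is carried out according to the protocol", and ten percent of the tapes are coded.

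**The concern.** The design compares a full program with a version lacking its specific ingredients. The result speaks to those ingredients only if everything else is alike. The plan matches the number and length of sessions, the maximum group size, the parallel parent groups and the session structure. It does not match who leads the groups, at least as described. The leader is the most direct carrier of warmth, empathy and positive attention, which are among the factors the plan says are comparable.

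At stake is the main conclusion, namely whether prevention for these children needs a trauma focus. If control therapists were more effective for reasons unrelated to content, a real content effect could be hidden. If they were less effective, an effect could appear that the content did not produce. The documents do not say which is more likely.

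**Working it through.** **Step 1. The descriptions side by side.**

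| Feature | Intervention | Control |
|---|---|---|
| Sessions | 9 of 90 minutes, parallel parent groups | same |
| Maximum group size | 8 | 8 |
| Program training and supervision | yes | yes |
| First therapist | social worker (usually) | clinical child psychologist or pedagogic specialist |
| Second therapist | mental health care professional (usually) | pedagogic specialist in training |
| Stated grade | none given | one of the pair is in training |

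Everything listed is matched except the therapist pair. The article does not describe therapists working in both arms or any matching of their background.

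**Step 2. Does therapist type follow the arm?** The Procedure section assigns whole groups to an arm, so each group brings its therapist pair into that arm. The association is strong as described. It is not shown to be total, because the intervention staffing carries the word *usually* and one of its categories is broad.

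**Step 3. Does a stated safeguard address it?** Of the two control variables, life events concern the family. Integrity concerns delivery of each program according to its protocol. Neither is described as a comparison of therapist type or therapist manner between arms.

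**Step 4. Illustration of size.** No figure in the article measures a therapist effect, so there is none to reproduce. The range below is assumed.

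Inputs from the sample size section: f = 0.25, two-sided alpha 0.05, 48 per condition. For two groups d = 2f = 2 × 0.25 = 0.5 SD.

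- Share of the planned effect: 0.1/0.5 = 20%; 0.2/0.5 = 40%.
- Standard error of the difference, plain two-group comparison in SD units: √(1/48 + 1/48) = 0.204.
- Probability of a significant result when the arms differ by b: Φ(b/0.204 − 1.96) + Φ(−b/0.204 − 1.96).

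*No content effect, staffing effect b only:*

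| b (SD, assumed) | b/SE | Chance of p < 0.05 |
|---|---|---|
| 0 | 0 | 5% |
| 0.1 | 0.49 | 8% |
| 0.2 | 0.98 | 17% |
| 0.3 | 1.47 | 31% |

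Under the 2:1 allocation in the Figure 1 legend, with about 93 and 47 of 140, the standard error is √(1/93 + 1/47) = 0.179. The chances for b = 0.1, 0.2 and 0.3 are then 9%, 20% and 39%.

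*True content effect of 0.5 SD with an opposing staffing effect, 48 per arm:* the net difference is 0.5 − 0.1 = 0.4 or 0.5 − 0.2 = 0.3. Power falls from 69% to 50% or 31%.

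The starting value of 69% is below the planned 80% because this is a plain two-group test. The planned 48 per arm fits a baseline-adjusted analysis with an assumed correlation of 0.5: n = 2 × (1.96 + 0.842)² × (1 − 0.5²)/0.5² ≈ 47.1, so 48. On that basis the standard error is 0.204 × √0.75 = 0.177. Power is then 81% without a staffing effect and 40% with an opposing 0.2 SD. A 0.2 SD staffing effect alone gives a significant result in about 20% of trials.

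These calculations ignore clustering by group. They show scale only and are not evidence that a staffing effect exists.

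**The case against.** The strongest reply is that different professions do not mean different warmth or different outcomes. The plan claims that both programs offer the same nonspecific elements; it does not claim the same disciplines. Both sets of therapists are trained in a standardized program and supervised. The plan also measures mediators tied to the taught content (emotion differentiation, coping, guilt, emotional security, parent-child interaction), which bear on whether an effect runs through that content. The 0.1 to 0.2 SD is assumed.

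Much of this stands. Shared training and supervision reduce the worry, and nothing in the article shows that staffing affects outcome. But comparability on nonspecific factors is asserted while their most direct carrier differs by arm, and mediator analyses do not remove confounding of the arm contrast.

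Four stronger readings are tempting, and the article does not support them:

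- *The confounding is complete and no analysis could ever separate the two.* The intervention staffing is only the usual one, and a mental health care professional could be a child psychologist.
- *Training level is known to differ.* A trainee is named in the control arm, but no grade is given for the intervention therapists.
- *Equality of nonspecific factors is never tested.* The article does not describe the coding sheet and may leave its items to a fuller document. One can say only that no stated check compares these factors between arms.
- *Similar warmth ratings would clear the way to credit the specific content.* A ten percent sample of tapes cannot show equivalence, and similar ratings would not remove the confounding.

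**Conclusion.** The concern holds in this form: therapist profession, as described, differs systematically by arm. Therapist type is therefore largely confounded with program content, and the stated control variables do not address it. The comparison of the two programs as randomized remains valid. What does not follow is the step from that comparison to the effect of specific factors.

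The size and direction of any bias are unknown. Under an assumed staffing effect of 0.1 to 0.2 SD, the distortion would be 20 to 40% of the planned 0.5 SD effect. The conclusion itself rests only on the two staffing descriptions, on assignment by group and on the stated aim, not on that assumption. It should be acted on because it changes what the trial can claim, and the remedy is cheap.

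**What to change.** No change of staffing is asked for; data collection is already in progress.

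1. **Rating.** Add a short rating of therapist warmth, empathy and positive attention to the coding of the integrity tapes already selected. Score it the same way in both arms and report it by arm as descriptive supporting evidence. Coders may recognize the arm from the session content, which should be stated.
2. **Staffing record.** Record each group's therapist disciplines and training levels, and report them by arm. This also shows how often the intervention departed from its usual staffing.
3. **Conclusion.** Word the primary conclusion as a comparison of the two programs as delivered, including their staffing. Name therapist type as an alternative explanation for any difference or lack of one. Do not use similar ratings as grounds for attributing the result to specific factors.

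The cost is a few extra items per coded tape, a simple record per group, and a more cautious headline claim.

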##### Children's sessions

In the children's sessions of the control program, a predictable and structured positive atmosphere is created. The control program follows a comparable structure as the intervention program: the children start in a circle holding hands, then they participate every week in a different fun activity. After that, children have a break and drink and eat something, listen to and discuss a short story about a topic unrelated to interparental violence or emotion recognition, and end with a gross motor game. At the end of the session, children are reunited with their parents and share their activities. The themes of the sessions are: 1) getting to know each other; 2) playing games; 3) healthy food and painting dinner plates; 4) decorating a name plaque; 5) relaxing: watching a movie/playing video games; 6) painting a club shirt; 7) scouting expedition; 8) making a goodbye movie, and 9) saying goodbye and evaluation.

##### Parents' sessions

To be able to relate changes in outcome measures to the content of the program, also nine parents' sessions have been developed for the control program. As in the children's sessions, the focus in the parents' sessions is on creating a positive atmosphere and having a good and relaxing time together. Topics of the sessions are: 1) getting to know each other; 2) fun things to do with your child(ren); 3) healthy food; 4) do-it-yourself; 5) books to read together with your child(ren); 6) how to keep a budget; 7) creative activities; 8) bingo, and 9) saying goodbye and evaluation.

### Measures

In this study primary outcome measures, mediating variables, moderating variables and control variables can be distinguished. The instruments include several questionnaires for both parent and child, and one for the teacher, two observational measures with parent and child, and an interview with the parent.

#### Primary outcome measures

The main research question of this study is whether children who experienced interparental violence benefit from participating in the intervention program in terms of less posttraumatic stress symptoms, less internalizing behavioral problems and less externalizing behavioral problems in comparison with children participating in the control program.

##### Posttraumatic stress symptoms of the child

To assess posttraumatic stress symptoms of children, parents are administered the Dutch translation of the **Trauma Symptom Checklist for Young Children (TSCYC) **[24]. This questionnaire consists of 90 items; parents rate the behavior and emotions of their child in the past month on a 4-point Likert scale, ranging from 'not at all' (1) to 'very often' (4). The TSCYC consists of eleven scales: two scales to assess the validity of the parent's answers (response level and atypical response), eight clinical scales (anxiety, depression, anger/aggression, PTSS-intrusion, PTSS-avoidance, PTSS-arousal, dissociation and sexual concerns) and a total PTSS score. The clinical scales of the TSCYC showed good reliability within a sample of maltreated children in the United States (Cronbach's α = .81-.91) [25] and in the Netherlands (Cronbach's α = .79-.91) [26].

To assess self-reported posttraumatic stress symptoms children are administered the Dutch translation of the **Trauma Symptom Checklist for Children (TSCC) **[27]. This questionnaire consists of 54 items, clustering in eight scales: two validity scales (underresponse, hyperresponse) and six clinical scales (anxiety, depression, anger, posttraumatic stress, dissociation, sexual concerns). The response categories are the same as in the TSCYC and reliability was high, with Cronbach alpha's ranging from .78 to .86 in a sample of sexually abused children [27]. In a sample of maltreated children in the United States TSCC showed discriminant and convergent validity with the TSCYC [28], and in the Netherlands TSCC showed convergent and criterium validity with other behavioral questionnaires (CBCL, TRF, YSR, CDI) [29].

##### Internalizing and externalizing behavioral problems of the child

Parents and teachers report about internalizing and externalizing behavioral problems of children using the **Child Behaviour Checklist (CBCL) **and the **Teacher Report Form (TRF) **[30]. Both parents and teachers are asked to fill out this questionnaire to collect information about the behavior of the child in two settings. The CBCL/TRF is often used in research on the effectiveness of programs for traumatized children [17,21] and has proven to be valid and reliable in research with normative and clinical populations. Cronbach alpha's for the broadband and total scales in a Dutch sample ranged from .78 to .93 for the CBCL [31] and from .86 to .96 for the TRF [32]. The CBCL consists of 113 items with which the parent rates the behavior of the child on a 3-point scale, consisting of 'not true'(0), 'sometimes true'(1) and 'very/often true' (2). The broadband scale 'internalizing problems' consists of anxiety/depression, withdrawal and somatic complaints subscales; the broadband scale 'externalizing problems' consists of aggression and delinquency syndrome subscales. Thought problems, social problems and attention problems make up the other subscales. All items can be summed to compute a 'total problems' score [30].

Children are administered the **Child Depression Inventory (CDI) **[33], consisting of 27 items to assess depression symptoms. Per item the child is asked to choose one of three sentences that fits best with his/her feelings and thoughts in the past two weeks. The child's answers are calculated into a total score (ranging from 0 to 54). The internal consistency in a Dutch sample was high (α = .79), just as the test-retest reliability (r = .79). The CDI has high criterion validity and scores on the CDI correlate highly with scores on other measures for depression [34].

